# Augmenting an online self-directed intervention for gambling disorder with a single motivational interview: study protocol for a randomized controlled trial

**DOI:** 10.1186/s13063-021-05912-3

**Published:** 2021-12-20

**Keywords:** Trial protocol, Self-directed intervention, Brief intervention, Problem gambling, Gambling disorder, Online intervention, Randomized controlled trial, Motivational interviewing

## Abstract

**Background:**

Despite the success of gold standard cognitive-behavioral therapy for problem and disordered gambling, the majority of individuals with gambling problems do not seek or receive professional treatment. Thus, the development of less intrusive self-directed interventions has been encouraged. Bibliotherapy for problem gambling has shown promise, both alone and in combination with motivational interviews, but there is still a lack of online self-directed intervention research. The current randomized controlled trial proposes to assess the additive benefit of a single digital motivational interview delivered in conjunction with an online self-directed treatment program for problem gambling and gambling disorder.

**Methods:**

A two-arm randomized controlled trial will be conducted, wherein eligible participants (*N*=270) will be recruited across Canada via internet advertisements posted to several platforms. All participants will receive access to an online self-directed gambling intervention program. Participants will be randomly assigned to either complete the online program alone or receive a digital motivational interview, conducted through an online audioconferencing platform (i.e., Microsoft Teams) to supplement the online program. The primary outcomes of gambling severity, frequency, and expenditures will be tracked along with secondary outcomes (i.e., depression, anxiety, general distress, alcohol use, and online program user data) over a 24-month period. It is expected that participants in both groups will experience a reduction in symptoms across the board, but more substantial improvements will be observed in the group that receives a supplemental motivational interview.

**Discussion:**

The results of this trial will expand upon prior gambling intervention research by informing best practices for the provision of online self-help for problem gambling.

**Trial registration:**

ISRCTN ISRCTN13009468. Registered on 7 July 2020.

**Supplementary Information:**

The online version contains supplementary material available at 10.1186/s13063-021-05912-3.

## Introduction

### Background and rationale

Most adults worldwide occasionally participate in some form of gambling, and this remains a leisure activity for them. However, some individuals’ gambling involvement escalates, and they continue gambling in an effort to recover their financial losses. Gambling disorder (GD) is diagnosed when persistent and recurrent gambling behaviors, such as chasing losses, lead to significant impairment or distress [1]. There are numerous ramifications following problematic gambling behavior at both individual and societal levels. For example, problem gambling often precedes financial strain, relationship difficulties, and criminal activity [2]. Additionally, those with GD experience a high level of comorbidity with mood, anxiety, personality, and other addictive disorders, as well as suicidality [3].

According to the diagnostic criteria in the *Diagnostic and Statistical Manual of Mental Disorders* (DSM-5), the lifetime prevalence of GD ranges from 0.4 to 1% [1]. In Canada and Alberta, past-year estimates of problem gambling approximate 2.4% and 2.8%, respectively [4]. Despite its high prevalence, as many as 85% of individuals with GD do not seek or receive professional treatment [5] for reasons such as shame, stigma, and a desire to solve the problem independently [6]. Considering the large proportion of those with GD who do not receive treatment, research into means of reaching this population without requiring extensive clinician contact has been encouraged.

Previously conceptualized as an impulse control disorder, GD is now included under non-substance-related addictive disorders in the DSM-5 [1]; thus, treatment regimens for GD are often grounded in models originally designed for substance-related addictions. Consistent with a stepped-care model of treatment for addictive disorders, a multitude of low-intensity interventions have been developed. Such interventions are intended to be minimally intrusive, yet allow for increasing intensity if necessary [7, 8]. For example, if non-assisted recovery fails (i.e., no intervention), treatment users have the option to progress to self-directed interventions (e.g., workbooks), brief interventions (e.g., motivational interviews), or more intensive interventions (e.g., weekly cognitive-behavioral therapies). In sum, this model allows for treatment to be tailored to individual needs without being overly intrusive.

Several self-directed interventions for GD have been established [7–9]. Notably, Hodgins and Makarchuk [10] developed a self-help workbook for gambling problems based on cognitive-behavioral principles. The activities within the workbook are organized into four modules: self-assessment, goal setting, goal implementation, and goal maintenance. Among other activities, workbook users are able to assess the frequency and severity of their gambling behaviors, set reduction- or abstinence-based goals, and plan for future urges, triggers, or potential relapses. This particular workbook has demonstrated efficacy in multiple trials [11–14]. The results of these trials suggest that the efficacy of this workbook is maintained even without any therapist contact (e.g., motivational interviewing), although the effects are not as strong.

In the first trial examining the efficacy of Hodgins and Makarchuk’s workbook [10], Hodgins and colleagues [13, 14] randomized participants to one of three trials: workbook-only, workbook plus telephone motivational interview, or a 4-week waitlist control condition. Follow-up assessments were conducted at 1, 3, 6, 12, and 24 months. Results indicated that both the workbook-only and workbook plus motivational interview groups experienced reductions in gambling frequency and severity compared to the waitlist control group at all time points except the 12-month follow-up. The improved outcomes were more substantial for the workbook plus motivational interview group. Although still significant, group differences were smaller at 6- and 24-month follow-ups compared to 1- and 3-month follow-ups [13, 14]. However, since differential gains were still observed at 24 months, the results suggest that the benefits of self-directed interventions are still apparent in the medium- to long-term, particularly when supplemented with a single session of motivational interviewing. Interestingly, a subsequent trial by Hodgins and colleagues [12] observed no incremental improvement in outcomes when additional motivational interviews were provided. These findings imply that a single motivational interview is enough to enhance the benefits of self-directed workbooks, and additional motivational interviews may not be necessary.

Internet interventions offer a cost-effective alternative to paper workbooks and traditional face-to-face interventions. Guided and unguided internet interventions have been largely successful when used to improve a variety of health conditions, such as diet, physical activity, tobacco use, and excessive alcohol use [15]. However, despite the promising development of self-guided paper workbooks for disordered gambling, both alone and in combination with other brief treatments, there is a lack of research exploring the impact of self-guided internet interventions in this area [16]. Of the research that has been done, much is not optimistic. Paradoxically, the lack of therapist contact, which was originally considered necessary to minimize in self-directed interventions, may be contributing to the deficits in treatment engagement [16]. The challenge that remains is providing sufficient therapist contact to facilitate treatment engagement without deterring a population that has strong preferences to limit such contact.

Previous research has combined self-guided internet interventions with brief therapist contact in the form of telephone instructions [17] or personalized feedback via email [18], but no significant effects were found. However, Carlbring and Smit [19] did find differential improvement when online self-guided treatment was paired with personalized emails and brief weekly phone calls providing instructions and support. Taken together, the literature suggests that therapist contact plays a crucial role in the recovery process, but the active component of contact comes in the form of brief support or the awareness that a professional is monitoring and encouraging their behavior changes.

### Objectives and major research questions

The primary purpose of this study is to expand the research on self-guided internet interventions for disordered gambling and explore whether they can have a more pronounced benefit when paired with minimal supportive clinician contact provided digitally. This contact will come in the form of motivational interviewing, which has been successfully paired with bibliotherapy in multiple prior trials [12–14] but has yet to be paired with online self-directed interventions for problem gambling. The specific objectives are twofold: (1) replicate, in the context of virtual care, the finding that supplemental motivational enhancement improves self-directed gambling treatment outcomes; and (2) test the hypothesis that supplemental motivational enhancement increases online self-help treatment adherence and engagement of individuals seeking treatment for gambling problems.

The current study will randomly assign participants to one of two conditions: internet workbook only (IO) or internet workbook plus motivational interview (IMI). In line with prior gambling intervention trials, primary outcomes will include gambling frequency, problem severity, and expenditures, while secondary outcomes will include measures of mental health, time spent on the self-help site, and participant feedback. The hypotheses for the current trial are:

#### Hypothesis 1 (H1)

Those in both the IO and IMI treatment conditions will experience a reduction in gambling frequency over the course of treatment. However, this reduction is expected to be more pronounced for those in the IMI condition.

#### Hypothesis 2 (H2)

Those in both the IO and IMI conditions will experience a reduction in gambling problem severity over the course of treatment. However, this reduction is expected to be more pronounced for those in the IMI condition.

#### Hypothesis 3 (H3)

Those in both the IO and IMI conditions will experience a reduction in gambling expenditures over the course of treatment. However, this reduction is expected to be more pronounced for those in the IMI condition.

#### Hypothesis 4 (H4)

Reductions in gambling frequency and severity for both the IO and IMI conditions will be positively correlated with time spent using the online self-help tools (i.e., more time spent online will be associated with greater reductions in gambling frequency and severity).

#### Hypothesis 5 (H5)

The IMI group will demonstrate greater adherence (i.e., more modules completed on the self-help website) compared to the IO group.

In addition to the four hypotheses listed above, one exploratory research question will be examined to determine the impact of each treatment condition on participants’ attitudes toward treatment. Attitudes are important to probe considering common pre-existing reluctance to engage in professional treatment in this population. The following research question will be examined:

#### Question 1 (Q1)

Will there be a difference in online workbook ratings between participant intervention groups?

## Methods

### Ethical approval and compensation

This study, including the methods and design, was approved by the University of Calgary Conjoint Faculties Research Ethics Board (CFREB), REB20-0568, in May 2020. Any modifications to the protocol, including changes to the objectives, design, sample size, or study procedures, will be agreed upon by all investigators and submitted for ethical review and approval prior to implementation. As of October 2021, two protocol amendments have been approved and implemented: (a) addition of a 24-month follow-up period to the existing 3-, 6-, and 12-month follow-up plan; and (b) requirement of MI session completion prior to, rather than following, the first CAD $10 compensation.

Participants will be financially compensated an electronic gift card valued at CAD $10 following: (1) confirmation of eligibility; (2) completion of the baseline assessment; (3) creation of an account with the online self-help program; and (4) completion of a motivational interview (if assigned to that group). Participants will also be remunerated with an electronic gift card valued at CAD $30 after each of four follow-up assessments have been completed in full; in total, participants could receive CAD $130 in electronic gift cards. Participants will have the ability to choose electronic gift card(s) from a number of local stores and restaurants. There is a possibility that some participants will sell their gift cards to finance gambling or otherwise take advantage of the compensation offered. We will mitigate this by screening for duplicate participants and using electronic (versus physical) gift cards.

### Confidentiality

Anonymity cannot be guaranteed, due to the use of email addresses (for online accounts and e-gift card compensation) and names to match interview data with online data. At the outset, participant data will be linked via personal information provided. Data from the online workbook will be linked with personal and survey data via unique participant identification numbers. Participants will be informed of these limits to anonymity during the consent process. After all data has been linked and participants have been compensated, personally identifying information (in a master spreadsheet) will be permanently deleted, with the exception of age and sex. This will leave only the anonymized data in an SPSS file. Participant data will be kept completely confidential unless there is (a) acute risk of harm to self or others (e.g., suicidal plans) or (b) court-ordered subpoena/other legal demands for data. If there is a high risk to self or others disclosed during an MI session, participants will be informed that members of the research team may contact local authorities or medical services to prevent harm.

### Participant recruitment and randomization

Participants will be recruited via targeted internet advertisements (i.e., “Are you concerned about your gambling? Study includes free and confidential online help for your gambling”). These advertisements will be distributed online (e.g., Facebook; Kijiji; YouTube; Google; Twitter; Reddit) to media users across Canada. To meet inclusion criteria, participants must (a) be a Canadian resident; (b) be 18 years of age or older; (c) have gambled at least once within the last month; (d) score 5 or more on the Problem Gambling Severity Index (PGSI) [20]; and (e) not currently be involved in treatment for their gambling. As with most prior gambling intervention trials, use of psychiatric medication will not be an exclusion criterion, but will not be assessed or monitored in this study. Prospective participants will be excluded if they are unable or unwilling to (a) provide their phone number and email address or (b) access the online program to create an account.

Individuals who are interested will be automatically redirected from a social media advertisement to an online eligibility screening questionnaire on Qualtrics. Those who are found to be ineligible will be thanked for their interest and directed to alternative resources for gambling help without any contact from the research team. Those who meet eligibility criteria will be automatically prompted to provide consent and contact information within Qualtrics, and then complete the baseline assessment. Qualtrics will be monitored daily for completed surveys that meet eligibility criteria and indicate consent. Eligible participants will be randomized by the research team to one of the two treatment groups and notified of their group assignment via email. Those selected to receive a motivational interview will also be invited to schedule their session. As previously mentioned, participants will not receive the initial compensation until the aforementioned steps have been completed. Those who complete at least one but not all of these steps will be sent a maximum of two reminder emails. Eligible participants can choose to be informed of the trial results via email upon its completion. Regardless, any publications and presentations resulting from this trial will be agreed upon by all investigators.

#### Participant validation

Email and IP addresses associated with survey responses will be checked for duplicates to ensure each participant only completes each survey once. Additionally, a VPN block and reCAPTCHA system will be implemented within each survey to prevent the enrolment of ineligible and fake participants, respectively. Finally, a randomly selected PGSI question will be presented at the end of the eligibility questionnaire; only participants whose response to this question matches the corresponding question in the initial set of PGSI questions will be enrolled.

Recruitment and retention of individuals seeking treatment for gambling problems can be a challenge. For example, a recent trial that assessed a brief versus extended self-directed online intervention found that only 66% of participants overall completed all three follow-up assessments. Furthermore, over 40% in the extended intervention never even accessed the self-help website [21]. To ensure an adequate number of participants are recruited and retained, this trial proposes to employ (a) nationwide recruitment; (b) compensation after the baseline assessment and each follow-up; and (c) multiple points of contact via email between participants and researchers. Additionally, engagement tends to be higher for briefer self-directed interventions (such as the current one) compared to extended self-directed interventions or professional treatment [21, 22]. Follow-up rates also appear to be higher when contact information beyond email addresses (e.g., phone numbers) are collected, as the least committed treatment seekers likely do not wish to provide this information [23]. Finally, the collection of participant feedback via the IEUQ survey can serve to guide the design of future online interventions for problem gambling such that attractiveness and uptake are maximized.

This protocol has been developed in accordance with the Standard Protocol Items: Recommendations for Interventional Trials (SPIRIT) statement. A randomized two-arm clinical trial will be conducted (see Table 1; Additional file 1). Participants will be automatically randomized in a 1:1 ratio to one of two groups: an internet only (IO) control group or an internet plus motivational interview (IMI) group. Group randomization will employ computer-generated minimization using the program MINIM [24] and stratified by sex (male; female; other), gambling severity (low-moderate; high), and whether they have been previously treated for their gambling (yes; no) based on stratification strategies used in prior trials [12–14]. Gambling severity, for the purpose of randomization, will be defined based on PGSI scores of low-moderate (score of less than 8) or severe (score of 8 or greater). MINIM will generate the allocation sequence, which it conceals until the moment of assignment (i.e., participant stratification data is entered and MINIM returns the group assignment for each participant individually at the time of assignment).

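### The duplicate check names email and IP address but not the mandatory phone number, so one person could be randomized twice; adding the number is a cheap improvement

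*Protocol article*

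**What the plan says.** Under Ethical approval and compensation, the Protocol article accepts that some people may abuse the payments and answers: "We will mitigate this by screening for duplicate participants and using electronic (versus physical) gift cards". It puts the most that one enrolment can earn at CAD $130.

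Under Participant validation it names what is compared: "Email and IP addresses associated with survey responses will be checked for duplicates to ensure each participant only completes each survey once". The same section adds "a VPN block and reCAPTCHA system will be implemented within each survey to prevent the enrolment of ineligible and fake participants, respectively". It also repeats one item of the Problem Gambling Severity Index (PGSI), so that "only participants whose response to this question matches the corresponding question in the initial set of PGSI questions will be enrolled".

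Under Participant recruitment and randomization, a phone number is a condition of entry in both arms: "Prospective participants will be excluded if they are unable or unwilling to (a) provide their phone number and email address". The benefit that the article claims for collecting it is retention: "Follow-up rates also appear to be higher when contact information beyond email addresses (e.g., phone numbers) are collected". The telephone is also the fallback for the interview. No section says that phone numbers are compared between records, and none says what happens to a record that shares an IP address with another.

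**The concern.** The check is described as ensuring single completion, but its two named identifiers cannot ensure that. A second email address is easy to obtain, and one person can have a different IP address at home and on a mobile network. The article holds a third identifier for everyone that is harder to multiply, and does not state that it is used.

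The trial's question is the difference between IMI and IO. A person present in both arms has had whatever treatment that person had, once, and reports much the same outcome under both records. Such a pair shows no arm contrast. It pulls the difference towards zero on gambling frequency, severity and expenditures, and likewise on modules completed (Hypothesis 5).

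**Working it through.** **Which stated safeguard would catch a real person entering twice?**
- Email match: not if a second address is used.
- IP match: not if a second genuine connection is used.
- VPN block: removes one easy source of a second IP address, but not a second real connection.
- reCAPTCHA: aimed at fake, automated entries; a real person passes.
- Repeated PGSI item: tests consistency within one record, not identity across records.
- Phone number: would match if reused, but is not named in the check.

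**Size of the dilution**

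Inputs: 270 records, 1:1 allocation (Protocol article). The planned total reproduces: 108 / 0.80 = 135 per arm, and 2 × 135 = 270. The article gives no duplicate rate, so the share f of records that are undetected second identities is an assumption, shown over a range.

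1. Second records: m = 270f.
2. If half the pairs split across arms, there are m/2 split pairs. Each puts one record in each arm, so the share of each arm made up of such records is (m/2)/135 = f.
3. If both records of a pair report the same outcome, the expected difference is (1 − f) times the true one. The shrinkage is f.

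- f = 2%: 5.4 second records, 2.7 split pairs, difference 2% smaller.
- f = 5%: 13.5 second records, 6.75 split pairs, difference 5% smaller.
- f = 10%: 27 second records, 13.5 split pairs, difference 10% smaller.

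**How much a phone check recovers**

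If a share r of the second identities reuse the phone number, the check recovers about r × f. With r unknown, this lies between 0 and f.

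**Standard error**

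Take identical outcomes within a pair.
1. Same-arm pairs alone: m/2 such pairs add 2 × (m/2)/270 = f to the relative variance of the difference. The true standard error is √(1 + f) times the reported one: 1.010, 1.025 and 1.049 for f = 2%, 5% and 10%.
2. Split pairs make the two arm means positively correlated. That takes 2 × (m/2)/270 = f off the relative variance.
3. Together: 1 + f − f = 1. When half the pairs split, the net error in the standard error is about zero.

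**The case against.** The strongest reply is that the article names two identifiers but does not say that others are ignored. Names are held for linkage (Confidentiality), surveys are monitored daily, and the research team enters each participant into the randomization program individually, so a repeat might be noticed anyway. A condensed article may leave the matching columns to a fuller document. This stands in part: a reader might infer that phone numbers and names are definitely never compared, and the article's silence does not prove that. But the article goes beyond silence, because it names the identifiers and says what they are meant to ensure.

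The incentive is also weaker than the total suggests. Of the CAD $130, $10 comes at the start and 4 × $30 = $120 depends on follow-ups completed out to 24 months. In IMI the first $10 also requires a recorded live call. This limits the likely number of duplicates. It does not remove a second record from the analysis, because participants who refuse the interview stay in their arm under intention to treat, and a split pair needs at most one call.

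The article mentions no verification of phone numbers, so someone set on a second identity could give another number. That stands, and it is why f is an upper bound on what the change recovers.

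A reader might also infer that genuine members of one household would be excluded for sharing a connection. The documents do not support this: addresses are checked, and no section says that an IP match leads to exclusion.

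**Conclusion.** The point holds as a cheap improvement to a safeguard that the plan itself relies on. It is not a contradiction or a numerical error. As described, the check would let one person with two emails and two ordinary connections be randomized twice, and records split across arms would dilute the IMI–IO difference by about f.

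That size rests on three assumptions: a duplicate rate that the documents do not give, half the pairs splitting, and the same outcome under both records. At low rates the effect is small, and a phone check recovers only the part of it where the number is reused. It might be tempting to add that duplicates make the standard errors too small. That is so for same-arm pairs taken alone, but split pairs offset it, so no net standard-error error is claimed.

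**What to change.** Under Participant validation, add the phone number, normalised to digits, to the email and IP check. Run the check before randomization and against all earlier enrolments. State that a match on IP address alone prompts a review and is not proof that two records are one person.

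Run the extended check once on the records already held, before the identifying information is deleted as the Confidentiality section provides. If matches are found, report a sensitivity analysis that keeps only the first record of each matched set.

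The cost is one more column in a check already planned, with no new data to collect. The downside is that an occasional shared household phone has to be resolved by hand.
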